#### Intervention group: Tai chi in addition to usual care

The Tai Chi intervention comprises 3 components: (1) Tai Chi classes, (2) home-based Tai Chi exercises, and (3) a behaviour change component (see logic model in Table 1). The intervention has been designed for participants to accrue 50 h or more of Tai Chi physical activity, because exercise-based interventions to prevent falls are more effective if: they have a higher dosage (50 h or more) and challenge balance (e.g. exercises are conducted while standing) [24]. To allow sufficient time for participants in the intervention condition to be allocated to a class and to complete the 20-week intervention, the post-intervention outcome assessments are scheduled 6 months post-baseline, to coincide with the end of the 20-week intervention period. Information about the Tai Chi exercise prescription and instructional methods are provided in Table 2.

**Table 1 Tab1:** Logic model of the TACIT Tai Chi intervention

Inputs	Activities	Outputs	Impacts	Outcomes

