*Human resources:* • Tai Chi instructors to deliver the intervention • Research team to make telephone calls to remind dyads to attend classes *Products:* • Booklet to support practice of home-based Tai Chi • Homework sheets to support practice of home-based Tai Chi • Alarm clocks to help remind dyads to practise Tai Chi at home *Estates:* • Venues in the NHS / community accessible by public transport and that have free car parking for hire of the Tai Chi classes	*Intervention contact:* • Weekly 90 min Tai Chi class for 20 weeks (45mins Tai Chi, 45mins socialising/Q&A with instructor) • A home visit by Tai Chi instructor in weeks 3–4 to support Tai Chi practice at home through behaviour change techniques (joint action & coping planning with carer) • Telephone contact by research team in weeks 2–18 to remind to attend classes if consecutively fail to attend 2 classes for unknown reason *Intervention led by carer:* • PWD to practise Tai Chi 20 mins per day • Daily self-monitoring & weekly instructor feedback: PWD to complete a daily diary of Tai Chi practised at home and hand to instructor at Tai Chi class weekly	• Joint action plan for practising Tai Chi at home • Joint coping plan for practising Tai Chi at home • Diaries of Tai Chi practised at home	• Increased participation in Tai Chi; physical activity designed to improve balance and prevent falls • Increased support to do Tai Chi via weekly instructor-led classes • Increased social support to practise Tai Chi through weekly contact with instructor and peers at the classes, and telephone reminders • Increased support to do Tai Chi at home via home booklet, homework sheets, action and coping planning, self-monitoring, instructor feedback, and alarm clock reminder	*Direct:* • Reduction in risk of falls via increased dynamic balance (postural stability) • Further reduction in risk of falls via: (a) increased functional balance (postural stability) (b) increased static balance (postural stability) (c) reduced fear of falls (d) delayed deterioration in global cognitive functioning (e) delayed deterioration in visual-spatial cognitive functioning • Reduction in risk of falls in the carer via: (a) increased dynamic balance (postural stability) (b) increased static balance (postural stability) *Indirect (*via *the above):* • Reduction in rate of falls • Increased quality of life • Increased quality of life in the carer • Reduced carer burden

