##### Tai chi classes

Each session will last for 90 min, with 45 min instructor-led group Tai Chi followed by up to 45 min informal discussion. Dyads will be encouraged to participate in the informal discussions each week to foster mutual peer support, and provide opportunity for ongoing advice from the Tai Chi instructor in relation to the home-based exercise component. Up to 10 dyads may attend per class. Teaching is based on implicit learning techniques, drawing on the Positive Emotion-Motivated Tai Chi (PEM-TC) approach developed in the USA [25, 26]. Through repetition of movements and positive reinforcement, this approach capitalises on PWDs’ capacity to continue to learn motor tasks with the use of muscle or kinaesthetic memory, i.e., unconsciously through making behaviours automatic, despite impaired ability to explicitly recollect such memories [25].

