##### Home-based tai chi exercises

Between the second and fourth class, the Tai Chi instructor will visit each dyad in their own home. Dyads will be given a pack containing a colourful home exercise booklet and weekly homework sheets, to serve as a reminder of what has been covered in the classes each week and to prompt practice of Tai Chi at home. The carers will be asked to facilitate the PWD to carry out Tai Chi for 20 min each day, at a convenient time and location. For safety reasons, dyads are asked not to practise Tai Chi at home until the Tai Chi instructor has made the home visit.

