### Assignment of interventions

In this trial we will aim to achieve equal balance of recruitment of participants between treatment conditions according to the following key prognostic variables: dementia type (due to eligibility criteria, this will be relatively homogenous in this study), age, fall history, and dementia severity. These are important variables because impairment in postural stability will be elevated among those who are older, have fallen in the past 12 months, and present with more severe dementia symptoms [19, 20]. Given that these key prognostic variables are positively correlated [19, 20], only one variable - fall history at baseline: has / has not fallen within the previous 12 months – was selected for a parsimonious and achievable strategy for balancing prognostic factors. The method of allocation needed to accommodate a trial design that allowed for variability in Tai Chi class size according to a dynamic recruitment process. Therefore, to ensure balance within each of the three treatment sites (and across the entire trial), minimisation will be used within each site to achieve a balance in fall history.

For each of the 11–15 classes, once a minimum of 4 dyads in total have been recruited, the dyads will be randomised to the intervention or control group. Random allocation will be achieved using a centralised automatic web-based randomisation system designed and maintained by the UKCRC-registered Peninsula Clinical Trials Unit (CTU). Once a minimum batch of 4 dyads has been recruited within a treatment site, the first dyad will be allocated using simple randomisation and the remaining dyads allocated using minimisation. Afterward, any further dyads recruited into the study before the fifth class has taken place will be randomised individually by minimisation and join the class if so allocated.

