#### Statistical methods

A detailed statistical analysis plan will be finalised separately before follow-up data collection is complete. Participants will be analysed in the group they are randomised to, and (with the consent of participants) we will attempt to collect complete data on everyone and use those data in the analyses. Descriptive statistics will be presented for all baseline outcome data for each trial arm separately. Descriptive statistics will be presented on the following for the PWD and their carer: gender, age, relationship status, current living arrangements, education level, ethnicity, previous experience of Tai Chi and treatment site. Additional descriptive statistics will be presented in relation to PWD: type of dementia, time since diagnosis, other long term conditions, existing injuries, use of a walking aid, number of medications currently taken, falls history (in past 12 months and past month), and current level of physical activity (moderate and vigorous).

Mean TUG scores at 6 months, the primary outcome, will be compared between the two trial arms using a mixed (multi-level) model approach to take into account clustering resulting from the group-based nature of the Tai Chi intervention. Baseline TUG, treatment site, and falls history in the past 12 months (Y/N) will also be included in the model. We will assume that the missing data mechanism is “Missing at Random” (MAR). No imputation methods will be used for the main analysis but will be explored in additional analyses. The method of analysis will be similar for other secondary outcomes for the PWD and carer. In addition, falls count data and the proportion of participants who fell will be analysed using negative binomial and logistic models respectively, taking into account falls history and treatment site. We will also conduct a per protocol analysis that will exclude participants from the Tai Chi group if they received fewer than 50 h (the intended minimum dose of the intervention).

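### The 50 h per-protocol cut-off asks for 88–96% of the prescribed Tai Chi, is out of reach on the prescribed schedule for some permitted late joiners, and is applied to one arm only

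*Protocol article*

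**What the plan says.** The primary comparison of Timed Up and Go (TUG) at six months keeps participants in their randomised arm. The Statistical methods section then adds: "We will also conduct a per protocol analysis that will exclude participants from the Tai Chi group if they received fewer than 50 h". It describes 50 h as the lowest dose intended, and it names no exclusion for controls.

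Four other places in the protocol article bear on this rule:

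- The section on the intervention group says the intervention was "designed for participants to accrue 50 h or more of Tai Chi physical activity".
- The Tai chi classes section says: "Each session will last for 90 min, with 45 min instructor-led group Tai Chi followed by up to 45 min informal discussion". Tables 1 and 2 give one class a week for 20 weeks.
- The section on home-based exercises asks for 20 minutes a day, but for safety "dyads are asked not to practise Tai Chi at home until the Tai Chi instructor has made the home visit". That visit falls between the second and fourth class; the Abstract and Table 1 put it in weeks 3–4.
- Assignment of interventions allows late entry for dyads allocated to Tai Chi: "any further dyads recruited into the study before the fifth class has taken place will be randomised individually by minimisation and join the class".

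The control group section sets a condition for controls too. They are asked not to start Tai Chi, Qigong, yoga or Pilates during the project.

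**The concern.** A per-protocol population should separate dyads who followed the prescribed intervention from those who did not. Here the cut-off lies just below the total that the schedule prescribes, so it may work as a test of near-complete adherence. It may also remove dyads for the date on which they were recruited and not for anything they failed to do.

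The exclusion acts on behaviour after randomisation, reported by the dyads themselves, and in one arm only. Those who keep up almost daily standing practice for months are likely to be fitter, better supported by the carer and less affected by illness or progression, and all of these also bear on TUG. Comparing them with every control gives up the protection of randomisation. The protocol says the trial is meant to inform a later definitive trial, so a flattering estimate of what Tai Chi does when it is practised could be carried forward.

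**Working it through.** **Inputs, all from the protocol article.**

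- Class time: 45 min = 0.75 h of Tai Chi a week for 20 weeks. The discussion period is not counted, because the stated dose is of physical activity.
- Home practice: 7 × 20/60 = 2.333 h a week, within the 20-week course.
- Home practice starts after the home visit. With the visit in weeks 3–4, this is taken as 2 to 4 weeks without home practice.
- Late entry is allowed up to class 5.
- Cut-off: 50 h.

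**1. The plan's own figure.** With d weeks before home practice starts, prescribed hours are 20 × 0.75 + (20 − d) × 2.333.

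- d = 2: 15 + 42.0 = 57.0 h
- d = 3: 15 + 39.7 = 54.7 h
- d = 4: 15 + 37.3 = 52.3 h

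All exceed 50 h, so the design statement is reproduced for a dyad that starts at class 1 and follows the prescription.

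**2. How close the cut-off is to that total.** 50/57.0 = 88% and 50/52.3 = 96%. The margin is 2.3 to 7.0 h.

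- All 20 classes attended: 35 h is needed at home; 35/42.0 = 83% to 35/37.3 = 94% of prescribed home practice.
- 80% of classes attended (12 h): 38 h is needed at home; 38/42.0 = 90% to 38/37.3 = 102%.
- Uniform 80% adherence: 0.8 × 52.3 = 41.9 h to 0.8 × 57.0 = 45.6 h; excluded throughout.
- Uniform 90% adherence: 47.1 to 51.3 h; excluded or retained according to the date of the home visit.

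If the visit is timed strictly by class number, so that only 1 to 3 weeks are lost, the total becomes 54.7 to 59.3 h and the cut-off 84% to 91% of it. The conclusion does not change.

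**3. Late joiners at full adherence.** A dyad joining at class j has w = 21 − j weeks left. With a wait of d weeks for the home visit, its prescribed hours are 0.75w + 2.333(w − d). The wait is not stated for late joiners, so a range is shown.

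| Joins at class | no wait | 1 week | 2 weeks | 3 weeks | 4 weeks |
|---|---|---|---|---|---|
| 2 | 58.6 | 56.3 | 53.9 | 51.6 | 49.3 |
| 3 | 55.5 | 53.2 | 50.8 | 48.5 | 46.2 |
| 4 | 52.4 | 50.1 | 47.8 | 45.4 | 43.1 |
| 5 | 49.3 | 47.0 | 44.7 | 42.3 | 40.0 |

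A class-5 joiner is below 50 h in every column. With no wait the sum is 16 × 0.75 + 16 × 2.333 = 12 + 37.3 = 49.3 h. Joiners at classes 2 to 4 pass or fail according to the wait.

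**4. The two arms side by side.** A Tai Chi dyad that departs from the prescription is removed. A control who takes up Tai Chi or similar exercise, against the request made of controls, stays in. Baseline TUG, if carried over from the primary model, would remove part of the difference between retained dyads and controls. It cannot remove selection on events during follow-up, such as illness or decline, that both reduce practice and worsen TUG.

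**The case against.** The strongest reply is that this analysis is supplementary. The primary comparison is as randomised, no conclusion is tied to the per-protocol result, and the Statistical methods section also plans to report classes attended out of those possible and home minutes out of those recommended, so readers will see the adherence data. This stands, and it limits the weight of the point.

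A reader might infer that many fully adherent dyads cannot meet the rule, that only a tiny subset would remain, or that most of the Tai Chi arm would be removed. The documents support none of these. Every fully adherent dyad starting at class 1 passes, and neither a number of late joiners nor an expected adherence rate is given. Late entry may be common: 75 Tai Chi dyads over 11–15 classes is 5 to 7 per class, while allocation can start with 4 dyads across both arms. But some of the later dyads may be allocated before class 1.

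Nor does a power calculation settle the matter. With the protocol's 4 s difference, an adjusted SD of 9.38 × √(1 − 0.7²) = 6.70 and 60 controls, power runs from 29% with 6 Tai Chi dyads retained to 86% with 45. Those numbers retained are assumptions, the sum supposes an unbiased effect, and the protocol's 90% belongs to the primary analysis.

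Three further replies have some force.

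- The hours above are prescribed amounts and not caps. A class-5 joiner with an immediate visit is 40 minutes short over 16 weeks, which a little extra practice would cover. But a per-protocol rule should not require more than the protocol prescribes.
- Counting the full 90 minutes of each session would raise the class-1 total to 67.3–72.0 h. That does not fit a dose defined as physical activity.
- Diaries are handed in at class, so a missed class might seem to lose recorded hours. Nothing says a diary cannot be returned later, and no weight is placed on this.

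**Conclusion.** The concern holds at moderate weight. The cut-off requires 88–96% of the prescribed Tai Chi from a dyad that starts on time. It excludes a fully adherent class-5 joiner in every case, and joiners at classes 2 to 4 in some. Because it is applied to one arm on post-randomisation, self-reported adherence, the comparison is selected and probably favours Tai Chi. The size of that bias, the number of late joiners and the share of the arm retained cannot be derived from the protocol.

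This rests on counting class Tai Chi time only, on home practice confined to the 20 weeks and begun after the visit, and on dyads following the prescription exactly. A reader might go further and take the trial's main result to be at risk. It is not, because the primary analysis keeps participants in their randomised arm and does not use the cut-off.

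**What to change.** Replace the one-sided exclusion with a complier-average causal effect analysis of TUG. Use randomisation as the instrument, the covariates of the primary model and allowance for class, and keep all participants in their randomised arm. Define compliance before the analysis plan is finalised, from the class registers and home diaries already planned, as a share of the dose offered to each dyad from its date of entry. Hours as a continuous exposure can serve as a sensitivity analysis, with the linearity assumption stated. Take control-arm uptake of Tai Chi as zero and say so, unless it is recorded; the protocol describes no such recording.

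If the 50 h comparison is kept, label it descriptive and do not count late joiners as non-compliant through their entry date alone.

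The passages on the design dose, the timing of the home visit, late entry and the per-protocol cut-off must be reconciled, including what counts towards the hours. No dose is proposed here.

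The cost is a change of wording and one further model, largely on data already planned. The interval will be wider than that of a simple per-protocol estimate. The exclusion restriction is also open to question: allocation to Tai Chi brings socialising, peer support and a home visit, and dyads classed as non-compliant may still benefit from partial practice. Both points should be stated with the result.

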Falls measurements will be collected prospectively from baseline until six months post-baseline. These include the number of falls by PWD (count data), the proportion of PWD who have fallen (binary outcome measure), and number of injurious falls (count data). The collection of falls data is in accordance with recommendations made by the Prevention of Falls Network Europe (ProFaNE) [38]. In our trial, the definition of a fall is, “an unexpected event in which the participants come to rest on the ground, floor or lower level” [38]. Falls will be recorded by dyads daily using prospective monthly calendars and returned on a monthly basis by post for data entry. Where falls are reported by dyads or calendars are not returned, a researcher will conduct a telephone interview to collect further information about the fall/clarify missing data. Telephone calls will be conducted weekly with the PWD as recommended for falls data collection with PWD [39]. In addition, to ascertain the accuracy of different recall periods, telephone calls about fall incidents by the PWD will be made monthly with the PWD and every 3 months with the carer. Fall injury will be recorded by telephone interview when recording falls as described above, using an existing set of definitions for severity of injury ([11, 40], p.).

Within the intervention group only, data will be collected half-way through the intervention on a 5-item questionnaire to ask about the importance of features of the intervention such as enjoyment of the classes and confidence in being able to continue to do the home practice. At the end of the final home visit, all dyads will be asked to complete a brief structured exit interview that asks about their hypothetical willingness to pay for the Tai Chi intervention should it be offered in the future as part of routine NHS care. The researcher will also ask participants if there have been any significant changes during the trial to their medical status (e.g. medication usage or elective surgery), which may influence performance on the primary outcome.

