One subgroup analysis is pre-planned for the primary outcome variable (TUG). Fall history at baseline (had a fall or not in the past 12 months), which is also the variable used for minimization in addition to treatment condition, will be entered as an interaction term in a statistical model (intervention effect x effect modifier). Departures from the proposed analysis, for example due to poor recruitment, will be explained and justified in the main trial paper. Feasibility objectives will be addressed by estimating recruitment and attrition rates (with 95% confidence intervals) and falls data parameters (falls rate, proportion of fallers, and completeness of falls data) for a future sample size calculation. In addition, we will compare the frequency of falls reported by each of the individual methods of data collection and their combination to determine if the increased resource in collecting falls data weekly provides more accurate data.

Descriptive data from the structured exit interviews will be presented on hypothetical willingness to pay for the intervention and perceived changes to health (PWD and carer). Data on number of Tai Chi classes attended and adherence to home practice will be presented. To assess adherence to the intervention in the Tai Chi arm we will calculate: adherence to classes (i.e. x attended out of y possible) and adherence to home exercise (i.e. x minutes exercise out of y recommended). The following data will not be reported in the main trial outcome paper but will be included in further secondary analyses in relation to visual spatial cognitive functioning (statue task); comparison of the different methods of data collection on incidence of falls; qualitative data; and uptake and adherence to the intervention (whether the PWD or carer had done Tai Chi before, mean (SD) intention and perceived behavioural control to do Tai Chi, and intervention group responses to the questionnaire delivered half way through the intervention).

Given the short-term (6-month) follow-up, low-risk intervention being tested, and no planned interim analyses, there will be no data monitoring committee for the trial. The trial will only be stopped early if the intervention is considered to be directly causing undue harm to patients as independently considered by the trial steering committee and/or NHS Research Ethics Committee.

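### Comparing how many falls each method reports does not show whether weekly calls are more accurate, and monthly calls are observed only in people who are also called weekly

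*Protocol article*

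**What the plan says.** In the protocol article, the Statistical methods section states the metric in its text on feasibility objectives: "we will compare the frequency of falls reported by each of the individual methods of data collection and their combination". The same sentence gives the purpose: "to determine if the increased resource in collecting falls data weekly provides more accurate data".

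The paragraph on falls in the Outcomes section, after Table 4, describes the sources:

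- Calendars: "Falls will be recorded by dyads daily using prospective monthly calendars and returned on a monthly basis by post for data entry".
- Weekly calls: "Telephone calls will be conducted weekly with the PWD as recommended for falls data collection with PWD".
- Monthly calls, added to the weekly ones: "to ascertain the accuracy of different recall periods, telephone calls about fall incidents by the PWD will be made monthly with the PWD".
- Carer calls: "every 3 months with the carer".
- Follow-up: "Where falls are reported by dyads or calendars are not returned, a researcher will conduct a telephone interview", in order to learn more about the fall or resolve missing data.

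The Statistical methods section also lists the comparison of methods among analyses to be reported outside the main outcome paper.

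**The concern.** The plan fixes both a metric (how many falls each method reports) and a conclusion to be drawn from it (which method is more accurate). The second does not follow from the first. A method's count is the true falls it captures plus any false or duplicate reports, and a total does not separate the two. The weekly and monthly informants are people with dementia, so reporting errors in either direction are plausible.

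The design adds a second difficulty. Monthly calls are meant to test a longer recall period, but they go to people who are also questioned weekly. No participants are described as receiving monthly calls only, so monthly recall without weekly calls is never observed.

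At stake is the reading of the result. A higher weekly count could be taken as accuracy when it is partly over-reporting. Similar counts could be taken as equivalence when they partly reflect carry-over. The trial is meant to inform a future falls-prevention trial, where weekly calling would be a real cost.

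**Working it through.** The article gives no figure for this comparison, so there is none to reproduce. It also gives no sensitivity, false-report rate or carry-over rate. All values below are assumptions chosen to show direction and range.

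**Step 1. Does frequency identify accuracy?**

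Reports per 100 true falls = 100 × (sensitivity + false or duplicate reports per true fall).

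Suppose weekly calls yield 90 reports and monthly calls 72, a ratio of 90/72 = 1.25. Take monthly sensitivity as 0.72 with no false reports. The weekly figure of 90 then fits each of these:

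| Weekly sensitivity | False or duplicate weekly reports per 100 true falls | Weekly reports | Weekly against monthly sensitivity |
|---|---|---|---|
| 0.90 | 0 | 90 + 0 = 90 | higher |
| 0.72 | 18 | 72 + 18 = 90 | equal |
| 0.60 | 30 | 60 + 30 = 90 | lower |

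The same frequencies fit weekly calls being more, equally or less sensitive than monthly calls. In the last two rows the share of weekly reports that are true is 72/90 = 0.80 and 60/90 = 0.67.

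**Step 2. What would carry-over do to the weekly-monthly gap?**

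Let weekly sensitivity be 0.90, let s be monthly sensitivity without weekly calls, and let p be the share of the falls that weekly calls would add which is then also reported at the monthly call. Assume no false reports.

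Observed monthly sensitivity = s + p × (0.90 − s); observed ratio = 0.90 / that value.

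With s = 0.60, the true ratio is 0.90/0.60 = 1.50:

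| p | Observed monthly sensitivity | Observed ratio |
|---|---|---|
| 0 | 0.600 | 1.50 |
| 0.25 | 0.675 | 1.33 |
| 0.50 | 0.750 | 1.20 |
| 0.75 | 0.825 | 1.09 |
| 1 | 0.900 | 1.00 |

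With s = 0.40 the ratio runs from 2.25 (p = 0) to 1.00 (p = 1); with s = 0.70, from 1.29 to 1.00. Carry-over can only narrow the gap in this model, and at p = 0 there is no distortion.

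**Step 3. The two together.** False or duplicate weekly reports raise the weekly count; carry-over raises the monthly count. They push the ratio in opposite directions, and frequencies alone do not show how much of either is present. If false reports are few, only the narrowing remains, so a weekly excess that is still visible would understate the true one.

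**The case against.** The strongest reply is that this is one sentence in a condensed article that defers to a separate statistical analysis plan, and that matching, de-duplication and the choice of a reference belong there. That stands for the missing detail, which is not the point made here. The point is that the article states an inference its stated metric does not support.

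A second reply is that the plan compares each method with the combination as well. A sensible combined count over overlapping sources needs reports of the same fall to be reconciled, and each method's share of it comes close to a capture rate. Reported falls also lead to a follow-up interview, which gives some check on false reports. Both stand as mitigation, but the article does not say that either feeds into the comparison.

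A third reply is that carry-over is assumed. That stands: it is inferred from the design, and the article's own account of impaired explicit recollection in this population suggests it could be small.

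Several stronger readings are tempting but unsupported:

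- A reader might infer that the comparison is worthless. It is not: it can describe added yield, and a higher weekly count is conservative evidence of better capture if false reports are few.
- A reader might infer that each monthly answer has been rehearsed about four times. The article does not say so; if each weekly call covers the preceding week, a given fall would be reported in one of them.
- A reader might infer that the calendar count absorbs falls learned by telephone. The article does not say that interview data are entered as calendar data.
- A reader might infer that this result will decide how the future trial collects falls. No decision rule is stated.

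**Conclusion.** The concern holds in a limited form. Frequency of reports does not identify accuracy, and the weekly-monthly contrast may be understated because the same people receive both calls. On assumed values, one observed ratio of 1.25 fits weekly sensitivity from 0.60 to 0.90, and a true ratio of 1.50 could be seen as anything from 1.50 down to 1.00. These are ranges of possibility, not estimates.

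The first part rests only on the definition of a count. The second rests on the stated schedule and on an unmeasured carry-over; it also assumes that weekly questioning does not make people report less at the monthly call. The between-arm falls models and the Timed Up and Go analysis do not depend on this comparison.

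**What to change.** Where the records allow, by date or by the details from the follow-up interview, match individual falls across the calendar as returned, the weekly call, the monthly call and the carer call, before any gaps are filled from another source. Use the reconciled combination as the reference, and report for each method:

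- the share of reconciled falls captured;
- the falls found by that method only;
- the unconfirmed or duplicate reports.

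Word the conclusion as the added yield of weekly calls rather than their accuracy. Falls missed by every source stay invisible, so the shares are relative to the combination. Matching does not remove carry-over either. The report should therefore state that monthly capture was observed after weekly calls and probably overstates what monthly calls alone would capture.

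The cost is some matching work and a more modest claim. Calls, visits and sample size do not change. Daily recording is explicit only for the calendars, and the article does not say whether the monthly and carer calls record dates, so how far matching can go should be checked against the records and reported.
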